### Participants

This study aims to recruit 30 PwP, which aligns with prior feasibility studies^43,44^ and will allow sufficient numbers for group exercise. Using convenience sampling, recruitment will be carried out in partnership with NHS consultant neurologists and geriatricians. The consultants will identify eligible PwP who meet the study inclusion criteria (Table 1) and will provide them with a participation information sheet *(Extended data*
^45^) and the principal researcher’s contact details. Those contacting the researcher will be given opportunity to ask any further questions and will be screened to ensure safety to exercise. PwP who are considered eligible will be offered an appointment within two weeks to undertake consent and baseline measures within their own home, prior to randomisation to either PDConnect or usual care (Figure 2).

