### Randomisation and blinding

Randomisation will be conducted by a Chartered Statistician independent to the study. Stratified random sampling by gender and physical activity will be employed to ensure balance at baseline. Using computer-generated random number sequencing (Excel, Microsoft Corporation) in a ratio of 1:1, a random number will be placed in a sealed, sequentially numbered, opaque envelope. PwP will be allocated randomly by extracting the random number from the envelope and will be notified of group allocation via letter. Group allocation will be concealed from the principal researcher until the end of the study, so that they remain blind to group allocation. Owing to the nature of the intervention being exercise, blinding of PwP is not possible. General Practitioners and Parkinson’s Consultants will be informed of their patients’ involvement within the study.

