#### Secondary outcome measurement

Although this study is not powered to detect statistically significant changes in clinical outcome measures, secondary outcomes (measured at baseline, at six, eighteen and thirty weeks) will be collected in order to provide some preliminary data on outcomes such as physical activity, motor and non-motor symptoms, depression and anxiety, fatigue, function, self-efficacy and quality of life. This will generate data on effect sizes to inform sample size calculation for a future effectiveness study. A suite of outcome measures will be employed in order to inform selection of the most appropriate measures for use in a future effectiveness study. All physical measures will be conducted by the principal researcher who is blind to the intervention allocation. Physical measures will be conducted using Microsoft Teams, with participants sent self-administered questionnaires in the post or online depending upon preference. Due to ongoing Covid restrictions, undertaking of physical measures face to face physical measures are not possible. Therefore, to maintain participant safety some physical measures will be omitted due to the online mode of delivery of this study imposed by Covid. This includes the Functional Gait Assessment, 6 minute walk test and the 10 meter walk test.

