### Planned data analysis

As this is an acceptability and feasibility study, the analysis will focus on the key parameters necessary for conducting a future trial. Most of the analysis will be descriptive in nature. The principal researcher will intelligently transcribe qualitative data from the semi-structured interviews. Participants will be sent completed transcribed documents to check for accuracy and make amendments or additions as required. Data will be analysed using NVivo version 12; following a framework analysis approach^62^ Coding and categorisation of data will be reviewed by a second researcher. Quantitative data including feasibility measures, demographic information, and baseline measures will be analysed using simple descriptive statistics using SPSS. Preliminary data will also be analysed to estimate the size of effect, by analysing the difference of mean change between PD Connect and Standard care at set points of six, 18 and 30 weeks. This will be calculated for each quantitative outcome measure (e.g. step count as measured by the fitness tracker, strength, balance, UPDRS, QoL) and will be established at each time point in order to calculate effect sizes and inform future sample size calculation. Further, this will inform the primary outcome for use in the future effectiveness study.

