### Monitoring

Analysis will be undertaken at set points during the study, following baseline measurements, and after the six, 18 and 30 weeks measurements are conducted. In a review of Parkinson’s clinical trials, Allen *et al*. (2012) reported that 69% of interventions retained 85% or more of their participants. Owing to the small sample size in the current feasibility study (n=30), an 85% retention rate has been set within the PDConnect study, with retention rate below this figure deemed as criterion for not progressing to a full trial. The target adherence for this study is set at 77% allowing participants to miss one physiotherapy session, and a maximum of three out of 12 weeks of group-based exercise. With exercise participation there is a potential falls risk. Within the activity dairy participants randomised to either arm of the study are asked to note all falls within their activity diary and contact the researcher directly to report any falls. A priori, more than five people reporting a falls during the intervention would trigger referral to the Data Management Committee (DMC) to discussion potential for study cessation. The DMC for this study aligns with the National Institute for Health Research Guidelines. The DMC will consist of four people who are independent to the study and institution where this study is being hosted. This will include a statistician, a Parkinson’s specialist clinician, a senior researcher, and a person with Parkinson’s. Meetings will be held annually, or more frequently if required, with a minimum quoracy for all meetings to be 67% (two thirds) of appointed members. The study will be monitored by all members of the project management group. They will oversee the conduct of the trial. As the sponsor, Robert Gordon University may request to audit processes and procedure, as will NHS Grampian who provide Research and Development (R&D) site approval for this study.

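### Between-arm effect sizes from about 13–15 people per arm are planned as input to the future trial's sample size and primary outcome, a use their precision cannot support

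*Protocol article*

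**What the plan says.** Under Planned data analysis, the protocol article will estimate the "difference of mean change between PD Connect and Standard care at set points of six, 18 and 30 weeks". This is to be done for each quantitative outcome measure and "established at each time point in order to calculate effect sizes and inform future sample size calculation". The next sentence adds a second use: "Further, this will inform the primary outcome for use in the future effectiveness study". On its natural reading, the subject of that sentence is the set of effect estimates just described.

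The section Secondary outcome measurement repeats the first use: "This will generate data on effect sizes to inform sample size calculation for a future effectiveness study". It also states that "this study is not powered to detect statistically significant changes in clinical outcome measures". The Discussion adds that effectiveness cannot be determined from this study.

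The sample size comes from precedent and from the needs of group exercise: "This study aims to recruit 30 PwP, which aligns with prior feasibility studies". No target difference is given, and no allowance for imprecision is attached to the planned use of the effect sizes.

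**The concern.** A pilot that cannot determine an effect is asked to supply that effect as a planning value. Two problems follow.

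- **Imprecision.** An effect estimated on about 26 to 30 people is compatible with a very wide range of true effects. The required sample size depends on the inverse square of the effect, so the error is magnified.
- **Selection.** The same estimates are to inform which outcome becomes primary. If a large observed effect counts in an outcome's favour, the estimate carried forward tends to be too large, and the next trial is then sized on it.

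What is at stake is the next trial. It could be too small, too large, or built on the wrong outcome. The article says its analysis concentrates on the parameters needed for a future trial, so this part of the output matters.

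**Working it through.** The plan states no power calculation, so there is no figure to reproduce.

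**Inputs from the protocol article**
- Total 30 (Participants), allocated 1:1 (Randomisation and blinding): 30/2 = 15 per arm.
- Retention threshold 85% (Monitoring): 15 × 0.85 = 12.75, about 13 per arm. This is the floor for progression, not a forecast.
- Measures listed under motor and non-motor function: UPDRS (counted once), Schwab and England, balance confidence, step count, apathy, anxiety, fatigue, depression, PDQ-39, Nottingham Health Profile, exercise self-efficacy and mental well-being. That makes 12.
- Three follow-up times: 12 × 3 = 36 estimates. The analysis section also names strength and balance, so the count could be higher.

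**Assumptions (not in the documents)**
- Two-sided 5% and 80% power for the future trial.
- True standardised effect d of 0.2 to 0.5.
- Correlation between outcomes of 0.3 to 0.7.

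**Precision of one estimate.** SE(d) ≈ √(2/n).
- n = 15: √(2/15) = 0.365; 1.96 × 0.365 = 0.72.
- n = 13: √(2/13) = 0.392; 1.96 × 0.392 = 0.77, or 0.81 with the t quantile on 24 df.

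An observed d of 0.3 with 13 per arm would have an interval of about 0.3 ± 0.81, that is −0.51 to 1.11.

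**Sample size on a fixed target.** n per arm = 2(1.96 + 0.842)²/d² ≈ 15.7/d². This gives 393, 175 and 63 per arm for d = 0.2, 0.3 and 0.5.

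**One outcome chosen in advance, observed d taken at face value (n = 13).**
- True power is below 80% whenever the observed d exceeds the true d, which happens about half the time.
- True power is below 50% when 2.802 × d/d_obs < 1.96, that is d_obs > 1.43d. The probability is P(Z > 0.43d/0.392), about 41%, 37% and 29% for d = 0.2, 0.3 and 0.5.
- The observed effect is zero or in the wrong direction with probability P(Z < −d/0.392), about 31%, 22% and 10%. No usable sample size then results, and a good outcome may be dropped by chance.

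**Largest of 12 outcomes at one time point, taken at face value (simulation, n = 13 per arm, same true d on all outcomes).**
- No true effect, correlation 0.5: the largest observed d averages 0.47.
- True d = 0.3, correlation 0.5: the median largest d is about 0.78. Then 15.7/0.78² = 25.8, so 26 per arm against 175 needed, with true power of about 19%.
- Over d = 0.2–0.5 and correlations 0.3–0.7: median true power is about 11–35%.

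**Largest of all 36 (4,000 simulated pilots per scenario, 13 or 15 per arm, true d 0.2–0.5, correlations from none up to 0.7 between outcomes and 0.8 over time).** Median true power is about 8–29%, so using one time point is the milder case.

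**The case against.** The strongest reply is that the text only says the estimates will inform the sample size and the primary outcome. A reader might infer that the observed effects will fix the sample size, that the largest will decide the primary outcome, and that the next trial will therefore probably be badly underpowered. The documents do not support that. No rule sets the sample size at the observed effect, and none selects the largest. The very low power figures need both steps. Without selection, the error can go either way: the next trial is about as likely to be too large as too small, and power below 50% is not the likelier result at any effect considered here.

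The plan also already collects much of what a sound choice needs. The Feasibility section covers retention, adherence and completion of outcome measures, and the Acceptability section adds interviews. The Secondary outcome measurement section says the suite is meant to help identify the most appropriate measures, which is not a largest-effect criterion. Effect sizes are secondary and labelled preliminary. Confidence intervals are a detail an article may leave to a fuller document.

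All of this stands, and it lowers the severity. It does not remove the point. The article states a use for the between-arm estimates that they cannot support, and attaches no limit to that use.

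**Conclusion.** The concern holds in a conditional form. The plan commits to letting very imprecise between-arm effects inform the next trial's sample size and primary outcome, against its own statements about what the study can show.

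The counts and the interval of about ±0.8 follow from the article's figures, and the one-in-two chance of falling below 80% power follows from treating a single estimate as the planning value. The 11–35% range is conditional on picking the largest effect at face value, and on the assumed true effects and correlations. It shows what the wording permits and is not a forecast.

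Severity is moderate. The primary feasibility and acceptability results, the retention criterion and the data collected are unaffected. What changes is what the pilot can properly hand to the next trial.

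**What to change.** Amend the Secondary outcome measurement and Planned data analysis sections to say that:

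- between-arm differences at 6, 18 and 30 weeks will be reported with 95% confidence intervals, as descriptive results only;
- the pilot will supply standard deviations, baseline–follow-up correlations, retention and completion for the future sample size, each with its uncertainty, since a standard deviation from about 26 people is itself imprecise;
- the future target difference will be a justified minimally important difference, not the effect observed here;
- the future primary outcome will be chosen on the completion and acceptability data already planned, on measurement performance (for example floor and ceiling effects and remote deliverability) and on relevance to participants, not on the size of the observed effect.

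The cost is wording and routine analysis, with no new data. The downside is that the pilot gives up its claim to supply a planning effect size, and the investigators must justify a target difference from elsewhere.

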### Monitoring

Analysis will be undertaken at set points during the study, following baseline measurements, and after the six, 18 and 30 weeks measurements are conducted. In a review of Parkinson’s clinical trials, Allen *et al*. (2012) reported that 69% of interventions retained 85% or more of their participants. Owing to the small sample size in the current feasibility study (n=30), an 85% retention rate has been set within the PDConnect study, with retention rate below this figure deemed as criterion for not progressing to a full trial. The target adherence for this study is set at 77% allowing participants to miss one physiotherapy session, and a maximum of three out of 12 weeks of group-based exercise. With exercise participation there is a potential falls risk. Within the activity dairy participants randomised to either arm of the study are asked to note all falls within their activity diary and contact the researcher directly to report any falls. A priori, more than five people reporting a falls during the intervention would trigger referral to the Data Management Committee (DMC) to discussion potential for study cessation. The DMC for this study aligns with the National Institute for Health Research Guidelines. The DMC will consist of four people who are independent to the study and institution where this study is being hosted. This will include a statistician, a Parkinson’s specialist clinician, a senior researcher, and a person with Parkinson’s. Meetings will be held annually, or more frequently if required, with a minimum quoracy for all meetings to be 67% (two thirds) of appointed members. The study will be monitored by all members of the project management group. They will oversee the conduct of the trial. As the sponsor, Robert Gordon University may request to audit processes and procedure, as will NHS Grampian who provide Research and Development (R&D) site approval for this study.

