### Physiotherapist/fitness instructors

Four NHS Physiotherapists will be recruited via purposeful sampling. Eligible Physiotherapists will have a minimum of two-years clinical experience including neurology and geriatrics. The Physiotherapists will be randomly assigned to deliver either PDConnect (n=2) or usual care (n=2), by the use of sealed envelopes provided by the research assistant. Two Fitness Instructors will be recruited from the University Sport facility and will be Register of Exercise Professionals (REPS) accredited (or equivalent). The two Physiotherapists and Fitness Instructors delivering PDConnect will participate in a blended learning training package aimed at developing expertise in exercise prescription for PwP and behaviour change techniques. Those physiotherapists delivering usual care will not receive any training.

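### Participants, who know their arm, report falls directly to what is very probably the blinded assessor, which puts the stated assessor blinding at risk

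*Protocol article*

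**What the plan says.** **Blinding.** Randomisation and blinding states: "Group allocation will be concealed from the principal researcher until the end of the study, so that they remain blind to group allocation". The same section says that "blinding of PwP is not possible".

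**Assessment.** Secondary outcome measurement states: "All physical measures will be conducted by the principal researcher who is blind to the intervention allocation". The remaining instruments reach the participant another way, with "participants sent self-administered questionnaires in the post or online depending upon preference". Step counts come from a wrist tracker and are written in the diary.

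**Falls.** Under Monitoring, participants in either arm note falls in their diary and are also asked to "contact the researcher directly to report any falls".

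**Timing of analysis.** Monitoring also says: "Analysis will be undertaken at set points during the study, following baseline measurements, and after the six, 18 and 30 weeks measurements" are done. Planned data analysis describes a comparison of mean change between PDConnect and standard care at set points of six, 18 and 30 weeks.

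**The concern.** Participants cannot be blinded, so blinding of the assessor is the main protection for the measures that the assessor conducts. The falls instruction opens a direct line, between visits, from people who know their arm to the person who must not know it. A natural account of a fall includes what the participant was doing and who was leading the session.

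Any leak would be selective. It would concern people who fall, and mainly those in PDConnect, because only that arm has features that identify it. Ratings of those people could then shift with the assessor's expectations.

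The affected measures are secondary, but they have a use. The article plans an effect size for each quantitative outcome to inform the sample size and the choice of primary outcome for a later trial. It also lists the feasibility of its testing procedures among the things to be assessed, so a weak point in the blind could be carried forward.

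Arm comparisons during follow-up would be a second and weaker source of expectation, if the assessor saw them.

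**Working it through.** The plan states no figure on this point. The check is a reading of sections side by side, followed by a count of the assessments that could be affected.

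**1. Who receives the fall call?** Monitoring says *the researcher*, not *the principal researcher*. Two other places settle the probable meaning.
- Participants: patients are given the principal researcher's contact details, and the next sentence speaks of those who contact the researcher.
- Fidelity assessment: the researcher does this work only once unblinded, so this is someone who was blind until then.

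The fall call therefore very probably goes to the blinded assessor. This is a strong inference, not an explicit statement.

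**2. What in a fall call would reveal the arm?** The PDConnect phases add up to 6 + 12 + 12 = 30 weeks.

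| Weeks | Usual care | PDConnect | What tells the arms apart |
|---|---|---|---|
| 1–6 | One-to-one online physiotherapy, home programme | One-to-one online physiotherapy, home programme | Little; the format is the same |
| 7–18 | No further sessions described | Weekly group class led by a fitness instructor, home programme | Mention of the class or instructor |
| 19–30 | No further sessions described | Independent home programme, monthly instructor call | Mention of the instructor |

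Mentioning a one-to-one session or the home programme does not separate the arms. Mentioning a class or a fitness instructor does, from week 7.

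**3. Which assessments could follow such a call?** The inputs are 30 participants, 1:1 allocation, and three follow-up waves (weeks 6, 18 and 30).
- Planned follow-up assessments: 30 × 3 = 90.
- PDConnect participants: 30 × 1/2 = 15, taking the arms as equal.
- Waves after week 7: weeks 18 and 30, so two.
- Ceiling for this route: 15 × 2 = 30 of 90 assessments.

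The ceiling would be reached only if every PDConnect participant gave the arm away in a fall call before week 18. A call between weeks 19 and 30 touches only the week-30 assessment. The article gives no expected number of falls, so no likely count can be derived.

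**4. Which outcomes are exposed?** Those that the assessor conducts, with the UPDRS as the plainest example. Posted or online questionnaires, tracker step counts, and the primary feasibility and acceptability outcomes do not depend on the assessor's blinding.

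**5. Interim comparisons.** Monitoring and Planned data analysis both speak of set points and share weeks 6, 18 and 30. Monitoring places analysis during the study. Together they appear to schedule arm comparisons after weeks 6 and 18. If the cohort moved in step, 30 × 2 = 60 of 90 follow-up assessments would come after the week-6 look and 30 × 1 = 30 of 90 after the week-18 look. With staggered entry, and complete waves awaited, fewer would remain. The independent statistician's only stated role is randomisation, and the article does not say who analyses the quantitative data or whether arm labels are masked.

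**The case against.** The strongest reply is that a reader might infer that the blind is bound to fail. The documents do not support that. A fall can be reported without naming the arm, and for the first six weeks the two arms have the same format. The text shows a risk, not a loss.

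A reader might also infer that the assessor will see interim results by arm. No section says so. The Monitoring sentence sits beside retention, adherence and falls, and does not itself mention a comparison of arms. The weeks in Planned data analysis could simply be the outcome time points. The promise that "Group allocation will be concealed from the principal researcher until the end of the study" points the other way. Who analyses the data, and under what masking, is detail that an article may leave to the full protocol. Group means also do not show which arm an individual is in; at most they raise expectations. All of this stands, and it reduces the interim point to a request for a safeguard.

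The falls threshold might be taken as a measure of how many people would be unblinded. It is a trigger for committee referral. It neither predicts a number of fallers nor says that each report reveals an arm.

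The stakes are also limited. The study is unpowered for clinical outcomes and disclaims any judgement of effectiveness. It protects the blind elsewhere, holding fidelity review until after unblinding and interviews until completion.

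The falls route is not answered by any of this. It is a written instruction that sits badly with the blinding statement, and it lacks the protection given to the fidelity review.

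**Conclusion.** The point holds as a risk to assessor blinding. The instruction on reporting falls, read with the sections on blinding and on secondary outcomes, sends participants who know their arm to the person who must not know it. The exposure is selective: PDConnect participants who fall and mention a class or an instructor from week 7 on. Its ceiling by this route is 30 of 90 follow-up assessments; the likely number is unknown and probably well below that. It affects assessor-conducted secondary measures, and through them the effect sizes meant for the later trial. It does not affect the feasibility conclusions.

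This rests on two readings: that *the researcher* under Monitoring is the principal researcher, and that reports sometimes describe the circumstances of the fall. The interim comparisons are a lesser part. They are plausibly scheduled while blinded assessments remain, with no statement that the assessor is kept from them, and they justify only a cheap safeguard.

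**What to change.** Two changes would reconcile Randomisation and blinding, Secondary outcome measurement, Planned data analysis and Monitoring.

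1. Name an existing team member other than the assessor to receive fall reports. One candidate is the research assistant, who already has a part in assigning the physiotherapists ("by the use of sealed envelopes provided by the research assistant"). The threshold for committee referral need not be touched.
2. Until the last week-30 assessment is done, limit interim looks to pooled retention, adherence and completion data. Alternatively, state that any arm comparison is run and held by someone other than the assessor.

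The cost is a new contact detail for participants, one amendment, and a small amount of work for existing staff. The article does not describe the research assistant's capacity, so that must be confirmed. If looks are pooled, early results by arm are forgone. No stated decision depends on them: the retention, adherence and falls criteria are not defined by comparing arms.
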